### Consent

Written informed consent from each participant is obtained. Precautions were taken to ensure participants’ privacy during data analysis.

### Data Collection Methods

#### Qualitative Data Collection

We will assess acceptability by qualitatively measuring how the intended target populations (grade 6 students, peer educator, peer leaders, teachers, and parents) react to the intervention. Feasibility of the intervention will be assessed by qualitatively measuring the reported experience of implementing the intervention by the target populations involved in implementing the project, such as the peer educators, teachers, and project staff. Evaluation of acceptability and feasibility will be performed at the end of the intervention (6 months from the start of the intervention).

We will collect data from purposively selected multiple sources using in-depth interviews, focus group discussions, and direct observation. Qualitative tools, such as in-depth interviews with grade 6 students, peer leaders, teachers, and parents will be used. We will conduct focus group discussions to collect data from peer educators. We will also use direct observation of the school environment and peer leaders’ interactions with the grade 6 students.

During the intervention, we will collect feedback from all participants and institutions after each class. Feedback content will be about the message quality, the instruction of the peer leaders, and the participation of students. Every step is closely monitored and audio or video recorded for analysis. A selection of students will also be invited to qualitative feedback sessions along with meetings with peer leaders weekly in the first month and each month afterwards.

#### Quantitative Data Collection

Dietary behaviors will be assessed using the validated Food Frequency Questionnaire developed for usage among junior high school students and used in previous studies. The secondary outcomes also include time spent on moderate-to-vigorous physical activity and time spent on sedentary behaviors among grade 6 students.

Time spent on moderate-to-vigorous activity will be assessed using the validated Physical Activity Questionnaire, and the time spent on sedentary behaviors will be assessed using the validated Sedentary Questionnaire that were used in previous studies among adolescents in Ho Chi Minh City [26,27].

#### Other Data Collected

Students’ standing height will be measured with a portable direct-reading stadiometer to the nearest 0.5 cm using the standard stretch stature method [28]. Body weight will be measured with shoes and heavy clothes removed using a Tanita electronic scale (Tanita BF 571, Tanita Corporation) to the nearest 0.1 kg. Anthropometric standardization exercises will be conducted by 2 trained data collectors using standard methods to ensure all data will be collected with uniform techniques and standardized measurement procedures [28]. The adolescent’s pubertal status will be self-assessed using a questionnaire with photographs illustrating 5 stages [29] of pubertal development for pubic hair, male genitalia, or female breasts; for female students, the date of their first menstruation is also recorded.

### Data Management

All quantitative data will be collected and entered using tablets at each school.

#### Statistical Methods

Analyses will be conducted using Stata 15 (StataCorp). Descriptive statistics will be used to describe the baseline characteristics of the sample. Feasibility and acceptability will be assessed following the evaluation plan described above. BMI will be calculated as weight in kilograms divided by the square of height in meters (kg/m^2^). The subjects were classified as overweight and obese by applying the age and sex-specific WHO BMI cutoff points [30]. Linear and logistic regression will be used to determine the effect of the intervention on the secondary outcomes, controlling for potential confounders (eg, sex, age, BMI).

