**Methods:**

The Peer Education and Peer Support (PEPS) project is a pilot cluster randomized controlled trial with 2 intervention and 2 control schools. The intervention consists of 4 weekly education sessions of why and how to choose healthy food and drinks and how to be more physically active. Additionally, the intervention includes a school-based and online support system to help maintain student engagement during the intervention. We will use in-depth interviews with students, peer leaders, teachers, and parents; focus group discussions with peer educators; and direct observation of the school environment and peer leaders’ interactions with the students. Acceptability and feasibility of the intervention will be assessed. We will also quantitatively assess limited efficacy by measuring changes in student’ physical activity levels and dietary behaviors.

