### Sample Size

The sample size for the qualitative assessments (feasibility and acceptability) is based on the principle of reaching data saturation. We will stop data collection and analysis at the point when no significant new data is generated. The quantitative assessments consist of approximately 200 grade 6 students, because we expect small follow-up losses and a likely high correlation between baseline and follow-up outcome measures.

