### Intervention Allocation

The assignment of participants to the intervention or control group is based on the location and population size of the school. There are 2 intervention schools and 2 control schools. We allocated the interventions at the school level, but the outcome assessments will be at the individual level.

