## Results

The first participant was enrolled in early September 2018. Recruitment was completed by March 2019. We delivered the peer education intervention at the start of each school year over 3 months for all new grade 6 adolescents in the allocated schools, followed by peer support and home engagement activities over 6 months until the end of the school year. However, the outcome assessments will be based on a cohort of adolescents only. There was a baseline assessment and 2 post-intervention assessments: the first immediately after the intervention to assess the short-term impact and the second at the end of the school year to assess the sustained impact on changes in adiposity, diet, and physical activity. In total, 326 grade 6 students were recruited. Data collection was completed in September 2019.

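### The only stated effect analysis for the secondary outcomes is student-level regression with no stated allowance for school-level allocation (2 v 2), so if followed as written it inflates the false-positive rate and gives intervals that are too narrow

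*Protocol article*

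**What the plan says.** The abstract (Methods) states that the project "is a pilot cluster randomized controlled trial with 2 intervention and 2 control schools". Under Intervention Allocation the article separates the two levels explicitly: "We allocated the interventions at the school level, but the outcome assessments will be at the individual level".

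Under Statistical Methods, one sentence fixes the effect analysis: "Linear and logistic regression will be used to determine the effect of the intervention on the secondary outcomes". The adjustment variables given as examples are sex, age and BMI, all student-level. Neither that section nor any other mentions clustering, an ICC, a design effect, a random school effect, a cluster-robust variance or a school-level comparison.

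The Sample Size section reads: "The quantitative assessments consist of approximately 200 grade 6 students". The reason given is "because we expect small follow-up losses and a likely high correlation between baseline and follow-up outcome measures", which also makes no allowance for clustering. The Results section reports the number reached: "In total, 326 grade 6 students were recruited".

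The regressions concern secondary outcomes only. The primary outcomes, acceptability and feasibility, are assessed qualitatively.

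**The concern.** Students in one school share teachers, a neighbourhood, a canteen and a sports timetable, so their diet and activity are likely to be more alike than those of students from different schools. Delivery by one dedicated team per grade 6 class adds a further possible source of likeness. A regression that counts each student as an independent observation takes its precision from the number of students, whereas the contrast between arms rests on four schools. Any chance difference between two pairs of schools can then be read as an effect of the programme.

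This matters even though the outcomes are secondary. These regressions are the only quantitative assessment of the intervention that the article states, measuring efficacy is part of the abstract's objective, and the Discussion says the findings will inform a larger cluster trial. An effect estimate with false precision could carry into that trial.

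**Working it through.** **The plan's own figure.** The target of about 200 students cannot be reproduced. The article gives no significance level, power, effect size, SD, ICC or design effect.

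**Inputs from the article.** Four schools, two per arm (Intervention Allocation); N of about 200 (Sample Size); N = 326 recruited (Results).

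**Assumptions.** Equal school sizes, so m = 200/4 = 50 or m = 326/4 = 81.5 students per school; ICC of 0.01, 0.02 or 0.05, since none is given.

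**Step 1, design effect.** DE = 1 + (m − 1) × ICC. For example, at m = 81.5 and ICC 0.02, DE = 1 + 80.5 × 0.02 = 2.61. The student-level analysis understates the standard error by a factor √DE.

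**Step 2, true type I error of a nominal two-sided 5% test.** 2 × [1 − Φ(1.96/√DE)]. For the same example, 1.96/√2.61 = 1.21, which gives 0.225.

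| N | ICC | DE | Effective N (N/DE) | True type I error | Simulated |
|---|---|---|---|---|---|
| 200 | 0.01 | 1.49 | 134 | 10.8% | 11.0% |
| 200 | 0.02 | 1.98 | 101 | 16.4% | 16.8% |
| 200 | 0.05 | 3.45 | 58 | 29.1% | 29.3% |
| 326 | 0.01 | 1.81 | 181 | 14.5% | 14.1% |
| 326 | 0.02 | 2.61 | 125 | 22.5% | 22.5% |
| 326 | 0.05 | 5.03 | 65 | 38.2% | 38.4% |

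The last column is from 4,000 simulated trials per setting with no intervention effect, analysed by a pooled student-level t test (school size rounded to a whole number). At ICC 0.005 the formula gives 7.9% (N = 200) and 9.8% (N = 326). At ICC 0, DE = 1 and the error stays at 5%.

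**Step 3, interval width at ICC 0.02 and N = 326 (163 per arm), in SD units, before any baseline adjustment.**

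- Ignoring clustering: 1.96 × √(2/163) = 0.22.
- With clustering and 2 degrees of freedom (four schools less two arm means; t = 4.303): 4.303 × √(2 × 2.61/163) = 0.77.
- Ratio: about 3.6, made up of √2.61 = 1.6 from the design effect and 4.303/1.96 = 2.2 from having only four schools.

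Over ICC 0.01, 0.02 and 0.05 the ratio is 2.7, 3.1 and 4.1 at N = 200, and 3.0, 3.6 and 4.9 at N = 326.

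**Step 4, does a school-level analysis repair it?** In the same simulations, a t test on school means with 2 degrees of freedom had a type I error between 4.6% and 5.5% in every setting.

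**The case against.** The strongest defence is that the article condenses a fuller plan. Its sentence names a family of models, its covariate list is open, and it states no variance estimator. Linear and logistic regression can carry a cluster-robust variance or a random school term, and the authors plainly know that allocation and assessment are at different levels. This stands in part. A reader might infer that the investigators have decided to treat students as independent; the document supports only that no allowance for clustering is stated. The point still holds, because the article names the model, its purpose and example covariates, and its sample-size rationale omits clustering too. The usual allowances would not rescue it automatically either: with two schools per arm, a robust variance or a random intercept without small-sample correction is itself unreliable.

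A reader might also infer that the analysis will produce false-positive effects. The document does not support that. The inflation depends on an ICC it does not give, and the article states neither a significance threshold nor a formal test. Adjustment for baseline may lower the ICC, and the ICC of a change score may differ from that of a single measurement. It does not follow that between-school variation disappears.

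A third tempting claim is that a permutation test of two against two schools cannot give a two-sided p-value below 2/6. That requires all six splits to have been possible. Study Settings places one central and one outlying school in each arm, and Intervention Allocation bases assignment on location and school size, so the figure has no support here.

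Finally, the affected outcomes are secondary and the abstract calls this part limited efficacy. That is correct and bounds the consequence: no conclusion on acceptability or feasibility depends on these regressions.

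**Conclusion.** The concern holds in this form: the stated analysis does not fit the stated allocation, and no allowance for school-level correlation is given. Applied as written, it inflates the false-positive rate for the secondary outcomes to roughly 11–29% at the planned size and 15–38% at the recruited size, for ICCs of 0.01 to 0.05. Its intervals are about 2.7 to 4.9 times narrower than a valid 2-degree-of-freedom interval over the same range. Much of that gap reflects the small number of schools, not the correlation alone.

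These sizes rest on assumed ICCs and an equal split across schools, and the half-widths are not those of the baseline-adjusted analysis. The direction needs only some between-school variation, and nothing in the article suggests that there is none. Correcting for clustering addresses precision only; it does not remove any bias from basing allocation on location and school size.

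**What to change.** Replace the sentence on linear and logistic regression under Statistical Methods with a two-stage school-level analysis, for example:

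> Each secondary outcome will be analysed in two stages. First, a linear (continuous outcomes) or logistic (binary outcomes) regression on the student's baseline value and the prespecified covariates will be fitted without a term for study arm. Second, the mean residual will be calculated for each school (for binary outcomes, the school-level proportion or residual), and the four school values will be compared between arms using a t distribution on 2 degrees of freedom. Results will be reported as exploratory estimates with 95% confidence intervals. No conclusion on efficacy will be drawn from statistical significance.

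Adjusting at student level in the first stage keeps the 2 degrees of freedom; a covariate entered at school level would use one of them. Working with school values also covers correlation within classes, since classes lie within schools.

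A random-intercept model should serve at most as a sensitivity analysis. With four schools its between-school variance may be estimated at zero, which returns the analysis to the student-level one, and the Kenward-Roger correction applies only to the linear outcomes.

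The change needs no new data, and since data collection is complete it concerns analysis and reporting only. Its cost is much wider intervals (about 3.6-fold at ICC 0.02 and N = 326), so most nominally significant results would be expected to disappear.

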#### Secondary Outcomes

Secondary outcomes consist of changes in dietary behaviors, including skipping breakfast, consuming soft drinks and fast food, and fruit and vegetable intake among targeted students (ie, grade 6 students). Dietary intake will be measured by a validated self-administered youth Food Frequency Questionnaire developed and validated in Ho Chi Minh City [24]. This questionnaire, which can be completed in 20 minutes, records the usual frequency of consumption over the past 6 months of 160 foods representing 8 groups: (i) processed foods; (ii) rice, breads, and cereals; (iii) meat, fish, and other seafood; (iv) fruits and vegetables; (v) sweets and snacks; (vi) milk and dairy; (vii) drinks; and (viii) miscellaneous. Information about breakfast and the frequency of out-of-home meals will also be collected.

Secondary outcomes also include time spent in moderate-to-vigorous physical activity as well as time spent performing sedentary behaviors among targeted students (ie, grade 6 students). Level of physical activity is assessed by the Adolescent Physical Activity Recall Questionnaire, which has been validated in Vietnamese adolescents [25]. Activities are assigned a metabolic equivalent score according to the compendium of physical activities. The Adolescent Sedentary Activities Questionnaire, which has good-to-excellent reliability and good face validity in Vietnamese adolescents, is used to measure sedentary behaviors including time spent watching TV, playing games, on the computer, doing homework, and performing sedentary hobbies.

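### The sample size leans on the baseline to follow-up correlation, but the effect model neither names the baseline outcome as a covariate nor says whether change or follow-up value is regressed

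*Protocol article*

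**What the plan says.** All references are to the protocol article.

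- **Sample Size.** "The quantitative assessments consist of approximately 200 grade 6 students", and the reason given is "because we expect small follow-up losses and a likely high correlation between baseline and follow-up outcome measures". Neither the loss nor the correlation has a number, and the section gives no effect size, SD, power or intraclass correlation.
- **Statistical Methods.** The model is stated as follows: "Linear and logistic regression will be used to determine the effect of the intervention on the secondary outcomes". The adjustment is then described by the words "controlling for potential confounders (eg, sex, age, BMI". The covariates are given as examples. The baseline value of the outcome is not among them, and no time point is given for BMI.
- **Form of the outcomes.** Under Secondary Outcomes, diet is framed as change: "Secondary outcomes consist of changes in dietary behaviors". Activity and sedentary behaviour are not: "Secondary outcomes also include time spent in moderate-to-vigorous physical activity as well as time spent performing sedentary behaviors". Quantitative Data Collection repeats the wording in terms of time. The abstract's Methods speaks of change for both activity and diet ("quantitatively assess limited efficacy by measuring changes in student", continuing to both), and the Results section speaks of change in adiposity, diet and activity. No section words sedentary time as a change.
- **Data and allocation.** The Results section reports one baseline and two later assessments, and 326 recruited students. Intervention Allocation assigns two schools per arm according to where they are and how large they are. Study Settings names different districts for each arm.

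**The concern.** A strong correlation between baseline and follow-up makes a small sample go further only if the analysis uses the baseline value, either as a covariate or through a change score. Here it is one of just two reasons offered for the sample size. Yet the only model statement in the article lists sex, age and BMI and leaves open whether the baseline outcome plays any part.

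A follow-up-only regression is therefore compatible with the text. It is most likely in two places: the activity and sedentary outcomes, which the outcome section words as amounts of time, and binary outcomes analysed by logistic regression. For a binary behaviour a simple change score is not available, so baseline status enters as a covariate or is lost. The article does not say which outcomes are binary; missing breakfast is a plausible example.

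The allocation raises the stakes. With four schools assigned by location and size, baseline differences in diet and activity between the arms are plausible, and the baseline outcome is the most direct measured guard against them.

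**Working it through.** **The plan's own figure.** The 200 cannot be reproduced, because the inputs are not given. The figures below are for orientation only.

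**Inputs.** From the article: N = 200 (Sample Size). Assumed: correlation r of 0.5 to 0.9, two-sided alpha 0.05, power 80%, 1:1 allocation by student, a baseline imbalance D of 0.2 SD, and equal SDs at baseline and follow-up. Clustering is ignored here and treated at the end. The variance factors apply to continuous outcomes.

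**Variance of the treatment comparison, relative to follow-up only**

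- Follow-up only: 1
- Change score: 2(1 - r)
- Baseline as covariate: 1 - r²

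The change-score factor exceeds the covariate factor by 2(1 - r) - (1 - r²) = (1 - r)², so the covariate model never has the larger variance. The ratio of the two is 2/(1 + r).

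| r | Follow-up only | Change | Covariate | Change / covariate |
|---|---|---|---|---|
| 0.5 | 1.00 | 1.00 | 0.75 | 1.33 |
| 0.7 | 1.00 | 0.60 | 0.51 | 1.18 |
| 0.8 | 1.00 | 0.40 | 0.36 | 1.11 |
| 0.9 | 1.00 | 0.20 | 0.19 | 1.05 |

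**Detectable difference at N = 200.** This is (1.96 + 0.84) × √(2/100) × √factor, in SD units:

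- Follow-up only: 0.396
- Change score: 0.307 at r = 0.7, 0.251 at r = 0.8
- Baseline as covariate: 0.283 at r = 0.7, 0.238 at r = 0.8

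Power for a difference of 0.3 SD at r = 0.8 is 56% (follow-up only), 92% (change) and 94% (covariate).

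**Bias from a baseline imbalance of D = 0.2 SD.** Suppose first that the imbalance regresses towards a common mean at rate r:

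- Follow-up only: rD = 0.7 × 0.2 = 0.14 SD at r = 0.7; 0.16 SD at r = 0.8
- Change: (r - 1)D = -0.3 × 0.2 = -0.06 SD at r = 0.7; -0.04 SD at r = 0.8
- Covariate: 0

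If instead the schools differ by a stable amount that persists in full, follow-up only carries D = 0.20 SD, change carries 0, and the covariate model carries (1 - r)D = 0.06 SD at r = 0.7. Under either assumption the follow-up-only analysis is the most exposed. Which of the other two is less biased depends on an assumption that the data cannot settle.

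**Clustering.** With 200/4 = 50 students per school and an assumed intraclass correlation of 0.01 to 0.05, the design effect 1 + 49 × ICC is 1.49 to 3.45, so 200 students are worth about 134 to 58 independent ones. The power and detectable differences above are therefore best cases. Covariate adjustment does not change that there are only four schools.

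**The case against.** The strongest objection is that the article nowhere excludes baseline. The covariates are only examples, and several sections describe the outcomes as changes. A change-score analysis uses the baseline and exploits the correlation; at the high correlation that the plan expects, it costs little (92% against 94% power at r = 0.8). A journal article may also leave the full covariate list to an analysis plan that is not shown, and these are secondary outcomes of a pilot. Finally, when schools are not assigned at random and the measures are self-reported, adjusting for baseline is not guaranteed to be less biased than change (Lord's paradox).

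Most of this stands. A reader might infer that the model omits the baseline outcome, or that the effects will be biased by 0.14 SD. The documents support neither: the first treats an open list as closed, and the second applies only to a follow-up-only analysis with an assumed imbalance and correlation. Nor can one say that a quantified precision was thrown away, since the Sample Size section quantifies none.

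What the objection does not remove is the mismatch within the article. The wording on change is not uniform, it never covers sedentary time, and it does not carry over to logistic models. The model statement does not settle which form is used. That is more than absent detail, because the sample size argument depends on the answer.

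**Conclusion.** The point holds as a failure to tie the model to the sample size rationale, not as a demonstrated omission of baseline. The article justifies about 200 students partly by a correlation that its stated model does not visibly use.

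The size depends on the reading. If follow-up values are regressed without baseline, the variance is about 2.0 times (1/0.51) that of the covariate model at r = 0.7 and about 2.8 times (1/0.36) at r = 0.8, and a 0.2 SD imbalance puts 0.14 SD or more into the effect at r = 0.7. If change scores are used, the excess variance is about 18%, 11% and 5% at r = 0.7, 0.8 and 0.9, and the remaining bias is about -0.06 SD at r = 0.7 under regression to a common mean. At r = 0.5, change scores gain nothing over follow-up only. Correlation, imbalance, alpha and power are all assumed. For binary outcomes the direction of the concern is the same, but these factors do not apply as they stand.

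It is worth correcting: the outcomes are secondary, but the findings are meant to inform a larger trial.

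**What to change.** In Statistical Methods, state that each secondary-outcome model regresses the follow-up value on arm and the baseline value of the same outcome (baseline status for binary outcomes), with sex, age and BMI measured at baseline. BMI needs the time point because the Results section treats adiposity as something that the intervention may change. Place this within an analysis that accounts for school; with four schools, one option is to adjust at student level first and then compare school-level mean residuals. Align the wording of the secondary outcomes with this choice.

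Report a change-score analysis of the continuous outcomes as a sensitivity check, because the schools were assigned by location and size. If the two analyses differ, say so and treat the effect as uncertain.

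The cost is a few lines of text and one extra analysis, since the baseline data are already collected. The change cures neither the clustering in four schools nor all confounding between them, and the report should say so.
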